#### Setting, participants and recruitment

We will select three organisational cases (care homes) for in-depth qualitative investigation through interviews with relevant stakeholders, aiming to explore the adoption, implementation and scale-up of VR training, as well as the impact on those delivering and receiving it, over time. The three care homes will include one of the small, medium and large care homes recruited through the trial.

Between 4 and 7 participants will be interviewed from each care home and will include staff who have taken part in the training. This could include staff from care homes in the intervention group, those in the control group, after having taken part in the training as part of the waitlist control or those involved in organising the sessions (eg, managers or senior carers).

We will purposively sample participants to ensure maximum variation in terms of individual and organisational contexts, considering potential adjustments to doses and configurations of implementation strategies necessitated by specific features of diverse implementation contexts. Recruitment will continue until data saturation is reached, with an estimated sample size of up to 20 participants (aiming for 14 learners and six managers/facilitators).

#### Procedures

The interviews will be conducted on-site at the care homes or remotely via telephone or Microsoft Teams, as convenient to participants. Interview schedules, developed in collaboration with the PPIE group, will be informed by using the NASSS framework^32^ and the CFIR,^33^ to uncover the underlying mechanisms driving the pilot RCT outcomes and to elucidate how the VR training might be adopted, implemented and scaled up. The interviews will be digitally recorded and transcribed verbatim for analysis.

#### Analysis

Transcripts will be uploaded to NVivo. The qualitative dataset will be analysed using thematic analysis, with some codes and categories developed inductively and others derived from NASSS, CFIR and literature on implementing VR training interventions (eg,^27^). Matrix analysis^47^ will be used to compare different respondent groups and organisations. This first phase of analysis will lead to the development of an analytical framework capturing the key determinants and mechanisms of a successful implementation and scale-up process. We will then synthesise the implementation-related insights gained from all research phases using the CFIR and NASSS to identify the ‘core enabling ingredients’ necessary to achieve sustained adoption and scale-up, as well as ‘adjustable elements’ that may vary across different implementation contexts. This blueprint will describe core barriers and enablers encountered, any variability in uptake that influences outcomes, any capacity for local adaptation, and the costs/resources necessary to embed and sustain the intervention in practice.

### Feasibility of conducting a full trial

This pilot study aims to explore VR training and develop the measures and methods to inform an RCT. We will, therefore, use a traffic light system to determine whether a full trial is feasible. Red indicates that it is not feasible (and that significant amendments are needed), orange that some improvements are needed, and green that it is feasible. We will map our findings to the criteria presented in table 3.

**Table 3 T3:** Pilot progression criteria to determine the feasibility of proceeding with a full-scale randomised controlled trial

Criteria	Interpretation
Care home sites recruited/opened	Red: 0–3 care homes (0%–50%) Orange: 4–5 care homes Green: 6 care homes (100%)
Willingness of care homes to be randomised	Red: 0–3 care homes (0%–50%) Orange: 4–5 care homes Green: 6 care homes (100%)
Retention of care homes at 3 months	Red: 0–3 care homes (0%–50%) Orange: 4–5 care homes Green: 6 care homes (100%)
Training completion (participants)	Red: 60%–74% Orange: 75%–99% Green: 100%
Retention of participants at 3 months	Red: Retain 60%–74% Orange: Retain 75%–79% Green: Retain ≥80%
Completeness of infections and falls data of residents at 3 months	Red: 60%–74% of residents Orange: 75%–79% Green: ≥80%

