#### Pilot cluster RCT

##### Setting, participants, recruitment and randomisation

Six care homes in North England will be recruited purposively to reflect the diversity of care homes in the UK. We will seek representation from care homes by different types (nursing, residential or mixed), size (number of beds), ownership (independent vs chain; private, charity or public) and location (deprivation).

We will recruit two small (1–50 beds), two medium-sized (51–100 beds) and two large (101–250 beds) care homes. A total of 80 staff will be recruited: 5 from each small care home, 15 from each medium home and 20 from each large home. The sample size has been selected to allow a sufficient number of repetitions of the protocols to identify any barriers and to permit assessment of feasibility outcomes.

Participants will meet all of the following inclusion criteria to take part:

Be an unregistered staff member employed at the care home, providing direct care to residents.Read and write in English.Not have previous health conditions that render them ineligible to use a VR headset due to safety reasons (eg, history of seizures).

Registered staff (eg, nurses), those unable to read/write in English or who do not provide care (eg, domestic staff or chefs) will be excluded. Randomisation will be stratified by the size of the care home, as measured by the number of beds (small (1–50 beds), medium-sized (51–100 beds) and large (101–250 beds)). Each study arm will contain one large, one medium and one small care home. All staff participants at a single site will be recruited before site allocation is revealed to ensure prospective concealment of the randomisation sequence. The randomisation sequence will be created by a study statistician, and each allocation will be revealed only after all staff participants at a site have been unambiguously enrolled in the study.

To reduce participant burden, all activities will be conducted during work hours (with the manager’s support) and on-site at the care homes, in private rooms. This may include an empty resident room, an activities room or a staff room. The researchers will be present on-site to conduct the study, meaning they can be flexible in rescheduling sessions if care work arises.

Staff will be recruited directly via the managers and senior care staff. They will identify all care staff who meet the eligibility criteria and will provide them with a written participant information sheet.

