**Feasibility outcomes**	
Trial feasibility	Recruitment and retention of sites and participants, as well as the number and % of staff trained. Reasons given for declining to participate (if applicable)
Training completion	Number and % of training sessions completed, and time taken
Observations	Qualitative observations (field notes taken by the researchers) on reactions, management policies, practices and care home culture and fidelity with the training schedule (considering the logic model from phase 1) to assess whether activities ran as planned
Cybersickness (post-training)	Validated and existing CSQ-VR^39 40^ to explore adverse effects related to using a VR headset (eg, fatigue or nausea)

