## Patient and public involvement and engagement

The project will be conducted with input from care home stakeholders, including several authors (JC, CC and VE), who contributed to the funding application and protocol and represent resident relatives and care home staff. The PPIE advisory group has now been broadened to include several care home managers and visitors to care homes. Contributors involved in direct resident care will provide insight into training delivery (and content) and the acceptability of VR technology in education for staff. Additionally, the PPIE group will also assist in recruiting participants, as buy-in from managers and staff is crucial.

The PPIE activities will be structured in accordance with the NIHR UK Standards for Public Involvement.^48^ The PPIE group will help design the training and toolkit, give insights on implementation, oversee the methods, review resources for readability, support recruitment, write lay summaries and coauthor publications. They will also be crucial to informing our wider dissemination plan and helping ensure the project has reach and impact. This is integral to the project due to the future impact on residents and workforce diversity. Participant resources must, therefore, be presented in an accessible manner to ensure inclusive recruitment. PPIE contributors will be given training by the research team to support skills and confidence to contribute meaningfully. We will use the NIHR INCLUDE framework^49^ to guide our PPIE work and participant recruitment, including the number of collaborators and representation (considering gender, age, ethnicity and work experience).

We have also linked in with the Adult Social Care Transformation Team, GM Integrated Care Partnership (ICP), who have identified care homes that want to be involved in the study. The GM Social Care Academy (part of the ICP) has also contributed to this protocol and is eager to support recruitment. Additionally, we have links outside of GM, including ICB links in Yorkshire and Humber, as well as care home networks in Merseyside and Cheshire. The team also has experience in working with the ENRICH network of research-ready care homes.

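### The progression table has no criterion for staff recruited, so all six rows can be green with well under half of the planned 80 staff enrolled

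*Protocol article*

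**What the plan says.** The pilot's recruitment plan is in the protocol article under Setting, participants, recruitment and randomisation (Pilot cluster RCT): "We will recruit two small (1–50 beds), two medium-sized (51–100 beds) and two large (101–250 beds) care homes", and "A total of 80 staff will be recruited: 5 from each small care home, 15 from each medium home and 20 from each large home". This size is justified on feasibility grounds, in part "to permit assessment of feasibility outcomes". Allocation is balanced by size: "Each study arm will contain one large, one medium and one small care home". The Abstract (Methods and analysis) gives the same 80 as a maximum rather than a target.

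Table 2 lists, under trial feasibility, "Recruitment and retention of sites and participants, as well as the number and % of staff trained", and also the reasons given for declining.

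Table 3 is the set of criteria to which the findings will be mapped to decide feasibility. It has six rows:

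- "Care home sites recruited/opened", "Willingness of care homes to be randomised" and home retention at 3 months. All three use the same bands: red 0–3, orange 4–5, green 6 homes.
- Training completion by participants: green at 100%.
- Participant retention at 3 months: red 60%–74%, orange 75%–79%, green 80% or more.
- Completeness of resident falls and infections data: same bands as participant retention.

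**The concern.** Table 2 names four things to track: recruitment and retention, each for sites and for participants. Table 3 grades three of them and leaves out participant recruitment. The two rows about staff start from people already enrolled, so a shortfall at enrolment does not pass through to either of them. The resident-data row does not depend on staff numbers at all.

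What is at stake is the decision to proceed. A cluster trial needs enough staff per home as well as enough homes. If homes open readily but few of their staff join, the sponsor needs to know before planning the full trial, and the stated rule could still return a feasible verdict.

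A smaller issue concerns the first two rows. They share the same 0–6 scale, and neither shows how many homes were approached and declined before opening. The PPIE section says a regional partner has already approached the sector and lists those "who have identified care homes that want to be involved in the study", so a count of six out of six says little about uptake among homes in general.

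**Working it through.** **Inputs.** Staff per home 5, 15 and 20 for small, medium and large, with two homes of each size and one of each size per arm (Setting, participants, recruitment and randomisation). Green thresholds from Table 3.

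**Step 1: reproduce the target.** 2×5 + 2×15 + 2×20 = 10 + 30 + 40 = 80. Per arm, 5 + 15 + 20 = 40. The stated figure is correct.

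**Step 2: apply Table 3 to an under-recruited pilot.** The scenario is illustrative: six homes open, accept randomisation and stay, each enrolling 4 staff.

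| Quantity | Calculation | Table 3 colour |
|---|---|---|
| Homes opened | 6 of 6 | Green |
| Homes willing | 6 of 6 | Green |
| Homes retained | 6 of 6 | Green |
| Training completion, intervention arm | 3×4 = 12; 12/12 = 100% | Green |
| Staff retained | 20/24 = 83% (threshold 0.80×24 = 19.2, so 20 needed) | Green |
| Resident data | assumed 80% or more | Green |
| Staff recruited | 6×4 = 24; 24/80 = 30% | No row |

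The example is not special. With 2 staff per home, 12/80 = 15% are recruited; 6 of 6 trained and 10 of 12 retained (83%) again give six greens. With 3, 8 and 10 staff per small, medium and large home, 42/80 = 52.5% are recruited, and 21 of 21 trained with 34 of 42 retained (81%) gives the same result.

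**Step 3: direction of the effect.** Green for training requires every participant to complete. If each completes independently with probability p, the chance of green is p^n for n intervention staff. Both values of p are assumptions.

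| p | n = 40 (target met) | n = 12 | n = 6 |
|---|---|---|---|
| 0.98 | 0.45 | 0.78 | 0.89 |
| 0.95 | 0.13 | 0.54 | 0.74 |

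Under-recruitment therefore goes unseen and also makes this row easier to pass.

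**Step 4: what a recruitment row would show.** Borrowing the 75% and 80% cut-points of the retention row: 0.75×80 = 60 and 0.80×80 = 64. On those cut-points 12, 24 and 42 staff would all be red.

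**The case against.** **The pilot will measure recruitment anyway.** This stands. Table 2 collects recruitment numbers and reasons for declining, and the process evaluation may ask which staff groups engage. A reader might infer that poor staff recruitment would go unnoticed; the documents do not support that. What is missing is a graded threshold in the table that decides feasibility.

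**The percentages might be meant out of the planned number.** Table 3 does not print its denominators. If retention were taken out of 80, the example would give 20/80 = 25%, which is not green. But that would no longer be retention in the ordinary sense, and nothing in the article suggests it.

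**Failed recruitment of homes would show.** This is correct: the first row turns orange at 4–5 homes and red at 3 or fewer. A reader might infer that all rows can be green whatever goes wrong with recruitment; that holds only for staff.

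**The willingness row is not a duplicate.** A reader might infer from the identical bands that the first two rows carry the same information and cannot register a refusal. The documents do not support this. Nothing says a home must accept randomisation before it opens, or that a refusing home is replaced. Staff are enrolled before the site's allocation is revealed, so a home could open, enrol and then refuse, and the two counts would differ. It is true that if willing homes are a subset of opened homes, and retained homes a subset of willing ones, the retention row alone fixes the worst home-level colour. That result comes from the assumed nesting and would make the first row just as dispensable. Separate rows still show where homes are lost.

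**Homes agreeing out of all homes approached is not willingness to be randomised.** This also stands. It mixes refusals of randomisation with refusals for lack of time, staffing or interest, and the homes are chosen purposively.

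**Conclusion.** The gap in staff recruitment is real. Table 3 can return six greens with 24 of 80 staff (30%), and with as few as 12 of 80 (15%), because participant recruitment is a listed feasibility outcome without a criterion. This is not detail left to a fuller document, since the article prints the progression criteria as a complete table. The conclusion rests on reading the training and retention percentages as shares of those enrolled, which is their natural meaning. The scenarios show what the rule permits; they do not predict what will happen.

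On the first two rows the supported point is limited: neither shows homes that declined before opening. The row on willingness can stay, with more reported beside it.

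**What to change.** 1. Add a row to Table 3 for staff recruited out of the target of 80, with bands fixed before phase 2 approval, which the article expects to seek at the end of 2026 or early 2027. For illustration, adapting the 75% and 80% cut-points of the retention row gives green 64 or more, orange 60–63 and red 59 or fewer. The printed red band starts at 60%, so extending red below that is an adaptation and not the protocol's own band. The orange band is only four people wide, and the sponsor may prefer other limits.
2. State 80 as the target throughout. The Abstract gives it as a ceiling, and a recruitment criterion needs a fixed denominator.
3. Beside the willingness row, report the number of eligible homes approached and the number that declined specifically because of randomisation, separately from those declining for other reasons.

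The cost is one table row, one wording change and a log of homes approached. Staff recruitment numbers and reasons for declining are already to be collected. The downside is that the progression result may look less favourable.

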## Patient and public involvement and engagement

The project will be conducted with input from care home stakeholders, including several authors (JC, CC and VE), who contributed to the funding application and protocol and represent resident relatives and care home staff. The PPIE advisory group has now been broadened to include several care home managers and visitors to care homes. Contributors involved in direct resident care will provide insight into training delivery (and content) and the acceptability of VR technology in education for staff. Additionally, the PPIE group will also assist in recruiting participants, as buy-in from managers and staff is crucial.

The PPIE activities will be structured in accordance with the NIHR UK Standards for Public Involvement.^48^ The PPIE group will help design the training and toolkit, give insights on implementation, oversee the methods, review resources for readability, support recruitment, write lay summaries and coauthor publications. They will also be crucial to informing our wider dissemination plan and helping ensure the project has reach and impact. This is integral to the project due to the future impact on residents and workforce diversity. Participant resources must, therefore, be presented in an accessible manner to ensure inclusive recruitment. PPIE contributors will be given training by the research team to support skills and confidence to contribute meaningfully. We will use the NIHR INCLUDE framework^49^ to guide our PPIE work and participant recruitment, including the number of collaborators and representation (considering gender, age, ethnicity and work experience).

We have also linked in with the Adult Social Care Transformation Team, GM Integrated Care Partnership (ICP), who have identified care homes that want to be involved in the study. The GM Social Care Academy (part of the ICP) has also contributed to this protocol and is eager to support recruitment. Additionally, we have links outside of GM, including ICB links in Yorkshire and Humber, as well as care home networks in Merseyside and Cheshire. The team also has experience in working with the ENRICH network of research-ready care homes.

## Ethical considerations and dissemination

###  Ethical approvals, considerations and mitigation strategies

The project will comply with ethical principles outlined in the Declaration of Helsinki.^50^ Two pathways for ethical approval will be taken due to different data being collected. The University of Manchester’s Proportionate Research Ethics Committee has approved phase 1 activities (Reference: 2025-24416-44642), and approval will be sought for phase 2 by the NHS REC through the Social Care Ethics Committee at the end of 2026/early 2027.

There are few risks and burdens to participating in this research, with the main burden being the time spent by participants during data collection. We will value participants’ time by conducting activities during work hours and compensating them with vouchers. Based on our previous studies, we have identified potential risks that may affect participants and researchers when conducting VR research in care homes (see table 4).

**Table 4 T4:** Ethical considerations and key mitigation strategies

Ethical considerations	Key mitigation strategy
Participant safety (harm)—experiencing cybersickness when using the VR headset	Participants will be provided with information at the beginning of using the VR training regarding symptoms of cybersickness, and if they feel uncomfortable at any time, we will stop the VR module, assist them in removing the headset and give them time to recover. Cybersickness symptoms cease promptly when the headset is removed We will use a variety of different headsets during phase 1 to identify if there is one headset that minimises cybersickness We have included a validated measure of cybersickness as part of our study outcome measures in phase 2 (the CSQ-VR)^39 40^
Participant safety (harm)—movement which has the potential for harming oneself on furniture	We will identify a space in each care home for data collection, which enables some degree of movement by participants We will remove all loose furniture prior to data collection starting and will have a researcher present to prevent participants from coming to harm Most VR headsets prompt users to create a boundary (ie, a safe area to use VR) and, when nearing this boundary, will automatically alert users and the headset camera will turn on, so the user will be able to see their physical position outside of the VR training
Researcher safety (harm)—lone working and travelling to unknown areas	Appropriate protocols from the University of Manchester will be followed to ensure checking in before and after data collection
Informed consent	We will strive to produce care staff-facing research materials in clear, lay language, as appropriate for individuals with limited literacy skills or who speak English as a second language. These will be sense-checked by the PPIE advisory group and informed by the Flesch-Kincaid readability metrics (aiming to score 60 or higher on the Reading Ease Score) Acknowledging that some people have not yet experienced VR, we will include photographs and a description of the technology in the information sheet
Coercion—power imbalance	Staff will be assured that they do not have to participate, and that non-participation will not impact their employment We will reassure all participants (and residents/carers) that no personally identifiable information will be published We will assure staff that their employment satisfaction data and behaviours related to hand hygiene and falls prevention will not be shared with their employer

CSQ-VR, 6-item Cybersickness in VR Questionnaire; PPIE, patient and public involvement and engagement; VR, virtual reality.

### Outputs and dissemination plan

We will work in collaboration with our PPIE contributors and stakeholders (eg, ICBs and care networks) to ensure we develop materials and plan dissemination activities that have the potential to reach the wider care home sector. We have used the 7Cs approach to guide our plan for impact,^51^ where we have identified the context, communities, constituencies and challenges we are addressing with the study. While we have some initial plans for producing outputs from our study and its wider dissemination, this will be revisited and developed throughout the study. We want to ensure that we are developing materials to communicate the findings from the study using appropriate methods for different audiences and the message we wish to communicate, and that we have appropriate measures for demonstrating that we have reached the desired audiences.

Outputs will include a user-friendly and acceptable VR risk reduction training programme for care homes, accompanied by an implementation toolkit adaptable for other VR training in social care settings. We will co-produce these materials with study participants and our PPIE group, and develop communication materials (eg, training overviews, infographics, YouTube videos) to help support the training tools.

Findings will be disseminated both nationally and internationally. They will be presented at relevant conferences and events, which are attended by managers, commissioners and resident relatives and published in journals. Lay summaries will be co-created with our PPIE advisory group, and additional dissemination methods will be co-developed to broaden reach. The lay summaries will be distributed to all interested participants and care home managers who have supported the project. A short report will be disseminated through the National Care Forum, reaching out to care homes across the country at the end of phases 1 and 2. A website for the project will be developed and will be updated on a regular basis with updates on research progression.

